### Economic analysis

Total costs will be estimated using a bottom-up (or micro-costing) approach, where information on each element of service used is multiplied by an appropriate unit cost and these are added to provide an overall total cost[32]. We will assess intervention costs, healthcare costs, patient and family costs, and costs outside the health care sector. For this study we will use a cost questionnaire especially designed for this group, based on existing questionnaires[28,29], which will identify all relevant cost aspects.

To measure the actual use of resources, data will be obtained using combined sources (registrations by professionals and cost questionnaire). Resources used relating to the interventions will be an estimation of the time spent by the professionals, based on prospective registration in a random sample. All use of resources by the patient and their family, in and outside the health care sector, will be measured by means of a cost questionnaire, in which the resource utilization is recorded at 12 weeks and 26 weeks during the follow-up period. These sources of information will be combined.

The valuation of healthcare costs and costs to patient and family will be based on the updated Dutch manual for cost analysis in healthcare research[33,34]. This manual recommends using standardized cost prices. In brief, the manual recommends that prices of informal care will be based on shadow prices for unpaid work (meaning a standard cost price based on general hourly wages). Costs of transport will be calculated as the mean distance per destination multiplied by standard cost prices. Costs of medication will be calculated using prices based on Daily Defined Dosage (DDD) taken from the Dutch Pharmacotherapeutic Compass[35], indicating the mean medication usage per adult per day. Productivity costs will be calculated by means of the friction costs method, based on a mean added value of the Dutch working population. The friction costs method takes into account production losses confined to the period needed (usually 90 days) to replace a sick employee. In case of uncertainty we will use a conservative estimation (i.e. the lowest cost price). Cost prices will be expressed in 2010 euros. If necessary, existing cost prices will be updated to 2010 using the consumer price index (CPI)[33,34].

Despite the usual skewness in the distribution of costs, arithmetic means are generally considered the most appropriate measure to describe cost data[36,37]. Therefore, arithmetic means (and standard deviations) will be presented. In case cost data are skewed, non-parametric bootstrapping will be used to test for statistical differences in costs between the intervention and control group. Non-parametric bootstrapping is a method based on random sampling with replacement based on the individual data of the participants[38]. The bootstrap replication will be used to calculate 95% confidence intervals around the costs (95% CI), based on the 2.5 th and 97.5 th percentiles. If cost data are distributed normally, t-tests will be used.

The incremental cost effectiveness ratio (ICER) will be determined on the basis of incremental costs and effects of the intervention compared to care as usual. The cost effectiveness ratio will be stated in terms of costs per outcome rate; the cost utility ratio will focus on the net cost per QALY gained.

The ICER will be calculated as follows. ICER = (Ci-Cc)/(Ei-Ec), where Ci represents the total costs of the intervention group at the 26-weeks follow-up, Cc the total costs of the care as usual group at the 26-weeks follow-up, Ei the effects at the 6-month follow-up for the intervention group and Ec the effect at the 26-weeks follow-up for the care as usual group. The robustness of the ICER will be checked by non-parametric bootstrapping (1000 times). Bootstrap simulations will also be conducted in order to quantify the uncertainty around the ICER, yielding information about the joint distribution of cost and effect differences. The bootstrapped cost-effectiveness ratio will be plotted subsequently in a cost-effectiveness plane, in which the vertical line reflects the difference in costs and the horizontal line reflects the difference in effectiveness.

The choice of treatment depends on the maximum amount of money that society is prepared to pay for a gain in effectiveness, which is called the ceiling ratio. Therefore, the bootstrapped ICERs will also be depicted in a cost effectiveness acceptability curve showing the probability that the intervention care is cost effective using a range of ceiling ratios.

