In 2006, these developments led to a redesign of the Stroke Service Maastricht Heuvelland. The essentials of this redesign are: stroke patients are admitted to Maastricht University Medical Centre for a maximum of 5 days for diagnosis, early intervention and stabilization, after which they are discharged to a special assessment and rehabilitation ward in a nursing home. In this nursing home, stroke patients undergo a structured multidisciplinary assessment, lasting a maximum of 5 days, and take part in their first rehabilitation activities. During assessment, the appropriate follow-up treatment is determined. Patients are then admitted to the follow-up setting for rehabilitative care. This means discharge to either their own home situation, to a specific rehabilitation hospital, or continued stay in the nursing home for prolonged rehabilitation or continuing stay.

Cost effective integrated stroke care requires a high degree of coordination between professionals in hospitals, nursing homes and home care, a high quality integral assessment in the nursing home and a system of adequately timed patient transitions.

The principal expectation is that the redesigned process of the Stroke Service Maastricht Heuvelland will lead to cost effective care, with expected improvement in the quality of care as well.

This article describes the design of a longitudinal comparative study, evaluating the cost effectiveness of an early discharge to and assessment of stroke patients in a nursing home, as part of a redesigned integrated stroke care programme, in comparison with a comparable stroke service region, where the redesign has not been implemented.

The research questions in this study are:

1. What is the effect of early admission to and assessment in the nursing home on functional outcomes, quality of life, and satisfaction with care in comparison with the usual care provided by a stroke service?[Effect evaluation]

2. From a societal perspective, what is the incremental cost effectiveness of early admission to and assessment in the nursing home, in comparison with the usual care provided by a stroke service?[Economic evaluation]

3. Research questions for the process evaluation

a) Is the new care pathway executed on time according to the protocol?[Process evaluation]

b) What are the experiences and opinions of patients and professionals about the newly developed care pathway?[Process evaluation]

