### Sample Size

The primary goal of this study is to achieve cost reduction without loss of quality of life. Based on an earlier study among stroke patients[10], we estimate a difference in utilities indicating health related quality of life between the 2 regions. In this earlier study by Olsen, the utility difference based on the EuroQol was 0.11. Based on a power of 80%, alpha 0.05, our study will need a sample size of 111 participants per group.

We expect a 25% drop-out of patients between inclusion and the follow-up meeting 26 weeks later, due to premature termination of the trial participation, inability to cooperate in the trial, or mortality[11]. To correct for this expected drop-out, the number of patients included will be increased to 139 participants per group.

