**Figure 1 F1:**
[figure not shown]
**Flowchart of the study**.

In the redesigned care pathway, after 5 days all stroke patients are discharged to a nursing home with a specialised assessment unit, resulting in a tailored rehabilitation programme. Only patients who can be discharged directly to their home within five days, or patients with complications requiring prolonged hospital care, will not be referred to the specialised nursing home unit. The nursing home physician examines each patient immediately on arrival in the nursing home and initiates the assessment program. In this program a multidisciplinary team, consisting of a psychologist, physiotherapist, occupational therapist, speech therapist, and trained nurses, examine the patient by means of a structured assessment protocol. Following assessment, the team will meet within five days of the patient's admission to make recommendations for the best rehabilitation program. Their advice will be based on admission and discharge criteria formulated by the various care providers participating in the stroke service. A structured possibility for the nursing home physician to consult a rehabilitation physician, if needed, is arranged. After the multidisciplinary meeting the patient and his family will be informed about the proposed rehabilitation track and after their approval this track can be started.

There are three options for rehabilitation after the assessment.

1. Rehabilitation at home with outpatient care provided by therapists from primary healthcare or day care rehabilitation in a hospital or nursing home

2. Inpatient rehabilitation in a nursing home

3. Inpatient rehabilitation in a rehabilitation centre

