### Usual care

The redesigned stroke service provided by the Stroke Service Maastricht Heuvelland, the intervention region, will be compared to "care as usual" provided by the stroke service in the Eindhoven area.

In the Stroke Service Eindhoven stroke patients are admitted to the stroke unit of the Catharina hospital in Eindhoven, where diagnostic tests, treatment and observation take place. During the patients' stay in the hospital, an assessment is performed in order to determine the best suitable rehabilitation facility for the stable patient. A physiotherapist, an occupational therapist and trained nurses carry out the assessment; if necessary they are supported by a speech therapist or a psychologist.

On the basis of admission and discharge criteria formulated by the various care providers who participate in the Stroke Service Eindhoven, the patient can be discharged to home, to a rehabilitation centre or to one of four nursing homes participating in the stroke service. The mean duration of the hospital stay in Eindhoven is 10 days. Consequently, the main differences in care arrangements between the experiment and the control region are the early hospital discharge and the structured assessment in the nursing home.

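### Taking the lowest unit price when a price is uncertain is not conservative for a cost difference between regions; it can bias the result either way, depending on which prices are uncertain

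*Protocol article*

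**What the plan says.** In the protocol article, under Economic analysis, costs are built bottom-up: "information on each element of service used is multiplied by an appropriate unit cost", and the products are summed. Healthcare and patient and family costs are valued from the Dutch costing manual, which recommends standardised prices. For prices that remain uncertain the rule is: "In case of uncertainty we will use a conservative estimation (i.e. the lowest cost price"). It is stated once, for all resources and both regions.

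The quantity of interest is a difference. The same section defines "ICER = (Ci-Cc)/(Ei-Ec"), so the cost difference between the regions is the numerator. The Sample Size section gives the hoped-for direction: "The primary goal of this study is to achieve cost reduction without loss of quality of life".

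The two pathways use resources in different proportions. Under Usual care the article sums up the contrast as follows (the sentence is cut one word before its end): "the main differences in care arrangements between the experiment and the control region are the early hospital discharge and the structured assessment in the nursing". On hospital stay, the Background says "stroke patients are admitted to Maastricht University Medical Centre for a maximum of 5 days", and Usual care says "The mean duration of the hospital stay in Eindhoven is 10 days". On nursing-home use, the Intervention section says "after 5 days all stroke patients are discharged to a nursing home with a specialised assessment unit", with exceptions for patients who can go straight home or who have complications. In the control region a nursing home is one of three discharge destinations.

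**The concern.** Taking the lowest price is cautious when the aim is to estimate the total cost of a disease without exaggerating it. Here the aim is to compare two pathways, and a cautious choice is then the one least favourable to the new pathway. Whether a low price meets that test depends on which region uses more of the item. The article applies one rule to all items and calls the outcome conservative, which is true for some items and false for others.

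The stake is how the base-case result is read. The Discussion treats proven cost effectiveness as a clear argument for wider implementation. A saving obtained with prices described as conservative would be taken as a lower bound on the saving, and the rule does not guarantee that. The planned bootstrap would not reveal the problem: it resamples patients and carries the chosen prices unchanged into every replicate, and so into the cost-effectiveness plane and the acceptability curve.

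**Working it through.** The article states no figure for this point, so there is none to reproduce. The check is on the sign of the effect, followed by an illustration.

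**Sign.** Let p be the unit price of an item, and q_i and q_c its mean use in the intervention and control regions. From the article's own cost construction:

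- Ci − Cc = sum over items of p × (q_i − q_c).
- If one price p is replaced by p × (1 − f), Ci − Cc shifts by −f × p × (q_i − q_c).

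The shift is negative, towards a saving, for an item the redesign uses more. It is positive for an item that control uses more.

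**Which items fall on which side, from the text.**

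- Hospital days: a maximum of 5 against a mean of 10, so control uses more. A low price works against the redesign.
- Nursing-home assessment stay: almost all intervention patients against one of three destinations in control. A low price favours the redesign.
- Assessment team: psychologist and speech therapist are standard members in the intervention, but join only when needed in control. A low price favours the redesign.

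**Illustration.** The article gives no prices and no total of nursing-home days. The following are assumptions: a hospital day costs 1 unit; a nursing-home day costs r = 0.4 to 0.6 units; the redesign uses d = 5 or 15 extra nursing-home days; the lowest price is f = 10% to 30% below the best estimate. Hospital use is taken from the text as 5 − 10 = −5 days, which compares a maximum with a mean and is only nominal.

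| Price set low | Formula for shift in Ci − Cc | d = 5 | d = 15 |
|---|---|---|---|
| Nursing home only | −f × r × d | −0.2 to −0.9 | −0.6 to −2.7 |
| Hospital only | +f × 5 | +0.5 to +1.5 | +0.5 to +1.5 |
| Both, same f | f × (5 − r × d) | +0.2 to +0.9 | −0.1 to −1.2 |

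End points, for example: 0.1 × 0.4 × 5 = 0.2 and 0.3 × 0.6 × 15 = 2.7. With both prices low, 0.3 × (5 − 0.4 × 5) = +0.9 and 0.3 × (5 − 0.6 × 15) = −1.2.

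The sign of the conclusion can change in either direction:

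- With d = 15 and r = 0.4, the best-estimate difference is −5 + 6 = +1.0, an extra cost. Setting only the nursing-home price 20% low shifts it by −0.2 × 0.4 × 15 = −1.2, to −0.2, an apparent saving.
- With the abstract's 12 days for the usual situation, the hospital difference is 5 − 12 = −7. The best-estimate difference is then −7 + 6 = −1.0, a saving. Setting only the hospital price 20% low shifts it by 0.2 × 7 = +1.4, to +0.4, an apparent extra cost.

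These values show that the direction is open. They do not estimate the bias in this study.

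**The case against.** The strongest defence is that the rule is symmetric: it treats both regions alike. If every price is understated by the same fraction f, then Ci − Cc shifts by −f × (Ci − Cc), so it shrinks towards zero and keeps its sign, which is cautious for a claimed saving. In the one-for-one swap above (5 fewer hospital days, 5 more nursing-home days) the net shift is indeed against the redesign. The rule is also only a fallback behind standardised manual prices and may touch few items. This stands in part. It rests on uniform uncertainty, which the article does not state. Where the redesign truly costs more, the same shrinkage understates the extra cost.

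A reader might go the other way and infer a net bias towards savings. The article ties healthcare and patient and family costs to the manual but names no price source for intervention costs, so the uncertain prices might be mainly those of the new assessment. The text does not establish this. It identifies no uncertain price; it says the intervention's staff time will be estimated from prospective registration in a random sample; and the same professions also appear in the control region's assessment.

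A reader might also extend the point to home care and informal care. The text gives no basis for that: home, nursing home and rehabilitation centre are destinations in both regions, no greater home or informal care under the redesign is described, and informal care has a standard shadow price.

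Finally, a journal article may leave the list of price scenarios to the fuller plan. Their absence is not the point here. The point is the rule that the article does state, and its label.

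**Conclusion.** The point holds as a flaw in a stated rule. A minimum price in the base case is conservative for items that usual care uses more and anti-conservative for items that the redesign uses more. On the text, the first group contains hospital days, and the second contains the nursing-home assessment stay and the full-team assessment. The incremental cost and everything derived from it can therefore be biased in either direction under a label that promises caution.

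The net direction and size cannot be determined from the article, because it does not say which prices are uncertain or by how much. The algebra rests only on the article's own cost construction and ICER formula. The assignment of items rests on its description of the two pathways. How many nursing-home days the redesign adds over 26 weeks is not stated, since later rehabilitation stays could differ either way. The effect may be small if the manual prices nearly everything.

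**What to change.** Replace the sentence on uncertain prices with a rule in three parts:

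- In the base case, use the best-estimate (mean or most likely) unit price for every item.
- In the sensitivity analysis, vary each uncertain price over a low and a high value.
- Define the conservative scenario as the one least favourable to the redesign: low prices for items used more in the control region, high prices for items used more in the intervention region.

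It would help to list the uncertain prices and their ranges before the regional costs are compared. The change costs one sentence and one extra sensitivity run, and needs no new data. The downside is that the reported cost difference may turn out less favourable to the redesign.

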### Economic evaluation

The economic evaluation compares costs and outcomes of stroke care given in the Stroke Service Maastricht Heuvelland to care as usual provided by the Stroke Service Eindhoven. The economic evaluation will involve a combination of a cost-effectiveness analysis (CEA) and a cost-utility analysis (CUA). In a CEA effects are presented in clinical outcomes.

The primary outcome measure of the cost-effectiveness analysis will be the SASIP-30. Within the cost-utility analysis, outcomes will be measured by means of the standard Dutch version of the EuroQol (EQ-5 D)[24]. This is a self-administered questionnaire, which will be completed together with the cost questionnaire at 12 weeks and 26 weeks.

Both generic quality of life, as well as utilities, will be derived by means of the EQ-5 D. The EQ-5D is chosen because it is a widely used quality of life instrument. The EQ-5D contains 5 dimensions of health-related quality of life; mobility, self-care, daily activities, pain/discomfort and anxiety/depression. Each can be rated at three levels: no problems, some problems and major problems. The 5 dimensions can be added to comprise an overall health state. This health state will be translated into a number, a utility. Utility values can be calculated for these health states, using preferences elicited from a general population, the so-called Dolan algorithm[25]. The utility values derived from the Dolan algorithm will be used to compute Quality Adjusted Life Years (QALYs). The Dolan algorithm has been established using a general population from the UK. Recently a Dutch algorithm has become available, and this will be used in the sensitivity analysis[26]. The utilities at the two time points are used to compute a Quality Adjusted Life Years (QALY) score by means of the area under the curve method. Furthermore, the EQ-5D consists of a visual analogue scale (VAS) ranging from zero (worst imaginable health state) to 100 (best imaginable health state). The reliability and validity of the EQ-5D has been established[27]. The primary outcome measure for the cost-utility analysis will be Quality Adjusted Life Years (QALYs), based on the EuroQol utility scores[24,27]. In the CUA, the incremental cost-effectiveness ratio (ICER) will be expressed as the incremental costs per QALY. This economic evaluation will be performed from a societal perspective, which implies that all relevant costs and outcomes will be taken into account.

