### Effect analysis

For the analyses we will use SPSS statistical software and Excel (for the Bootstraps). Missing data on the item level will be handled using SPSS missing value analysis. If considerable data are missing related to specific instruments, imputation will be considered.

A baseline analysis will be performed to examine the comparability of groups at baseline for both costs and outcomes. If necessary, methods will be applied to correct for differences in baseline[30]. A Kolmogorov-Smirnov test will be performed to investigate whether the data are normally distributed. If the data are distributed normally, our primary analysis will start with a t-test. If data are skewed, the primary analysis will be based on a non-parametric test for assessing two independent samples, i.e. a Mann-Whitney U test.

As it is known that in non-randomised comparative studies, variations in case mix between centres can influence the interpretation of outcome data[31], we would like to explore this in further analysis. Therefore, for each of the data sets collected at all measurement points, differences in outcome variable between the 2 regions will be tested using multiple MANCOVAs, entering various indicators of case mix as co-variates, i.e. age, gender, stroke severity. In addition, information on possible confounding factors and effect modifiers will be collected and analysed.

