## Discussion

Implementation of the redesigned stroke care pathway in the Stroke Service Maastricht Heuvelland started in 2006. It has yet to be seen whether the introduction of this care pathway has led to improvement of the quality of care for stroke patients. The results of this study will provide information about the cost effectiveness of the intervention and its effects on clinical outcomes and quality of life. In this respect the relevance of this study lies in the fact that it is one of the first studies assessing the cost effectiveness of a stroke service from a societal point of view. In case of proven cost effectiveness, arguments for implementing the intervention into usual healthcare are clear and evident.

A weak point of this study is the possible bias of non-randomisation. In our study randomisation is impossible as the location of the stroke patient necessarily determines to which hospital the patient will be admitted, and in order to prevent contamination effects, only one treatment will be offered in one hospital. If our intervention appears to be cost effective, the next step will be broader implementation in more nursing homes. In addition, it will be possible to perform a cluster randomised trial to obtain even more evidence on the effectiveness of the interventions. A strong point of the study is the standardised and consequent use of validated measurement instruments, which make the characteristics of the study population accessible for further studies.

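### The economic analysis of this non-randomised comparison specifies no case-mix adjustment, and the planned baseline correction has no baseline cost, EQ-5D or SA-SIP30 to work with

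*Protocol article*

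**What the plan says.** All references are to the protocol article.

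- **Cost comparison (Economic analysis).** For costs, "arithmetic means (and standard deviations) will be presented". If costs are skewed, "non-parametric bootstrapping will be used to test for statistical differences in costs between the intervention and control group", with percentile 95% limits. If they are normal, t-tests are used.
- **ICER (Economic analysis).** The ratio is "determined on the basis of incremental costs and effects of the intervention compared to care as usual". The formula given is (Ci − Cc)/(Ei − Ec), where the terms are each group's total costs and effects at 26 weeks. It is bootstrapped 1000 times, and the replicates feed the cost-effectiveness plane and the acceptability curve. No covariate, regression or weighting is mentioned.
- **Case mix (Effect analysis).** Differences between regions in the outcome variables are explored with MANCOVAs that include age, gender and stroke severity.
- **Baseline check (Effect analysis).** The groups are to be compared at baseline on costs as well as outcomes, and then "If necessary, methods will be applied to correct for differences in baseline".
- **Timing (Economic evaluation).** The EQ-5D is a questionnaire "which will be completed together with the cost questionnaire at 12 weeks and 26 weeks". Table 1 agrees, and it also shows SA-SIP30 only at 12 and 26 weeks.
- **Stated limitation (Discussion).** "A weak point of this study is the possible bias of non-randomisation".

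**The concern.** The Sample Size section gives the primary goal as reducing costs without losing quality of life, and the Discussion would use proven cost effectiveness to argue for implementation. The economic comparison therefore carries the main conclusion. It is also the one part of the quantitative analysis for which no case-mix adjustment is written down, although the article accepts that case mix between centres can affect how outcomes are interpreted.

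Stroke severity and age can plausibly affect length of stay, nursing-home use and utility together, so an imbalance between regions could move both the numerator and the denominator of the ICER. Imbalance is also plausible from the eligibility rules. Patients who go home within a few days, or who need prolonged hospital care, are excluded, and hospital stay differs between the regions by design. That is an inference from the criteria, not something the article reports.

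If such an imbalance exists, a percentile interval or an acceptability curve would describe precision around a confounded difference.

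**Working it through.** The plan states no figure for this point, so the check has two parts: the planned methods against the measurement schedule, and an illustration of size.

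**1. Methods against schedule**

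| Quantity | Use | First measured | Adjustment stated in Economic analysis |
|---|---|---|---|
| Costs | ICER numerator | 12 weeks | none |
| EQ-5D utility (QALY) | CUA denominator | 12 weeks | none |
| SA-SIP30 | CEA denominator | 12 weeks | none |
| Age, sex, socio-economic status, co-morbidity, NIHSS | background variables | baseline | not carried in |
| Barthel, modified Rankin | outcomes | T0 | not carried in |

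None of the three quantities behind the two ICERs has a scheduled baseline value. The professional registrations in the Economic analysis section record staff time on the intervention in a random sample. The cost questionnaire records use during follow-up. Neither is described as giving costs before the stroke. The promised baseline comparison of costs therefore does not fit the schedule. The variables in the last two rows are available for adjustment.

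**2. What a two-group comparison does under imbalance**

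Assumptions, none of them from the article: the regions differ by d SD in severity, severity correlates r with cost, and there is no true cost difference.

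- Bias of the unadjusted difference, in SDs of cost: b = d × r.
- Standard error in SDs: √(2/n), with n per group.
- Two-sided rejection rate at nominal 5%: Φ(b/SE − 1.96) + Φ(−b/SE − 1.96).

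With the planned 139 per group and 25% drop-out, n = 139 × 0.75 ≈ 104 and SE = √(2/104) = 0.139.

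- d = 0.2, r = 0.4: b = 0.08, shift 0.08/0.139 = 0.58, rejection 8.9%.
- d = 0.3, r = 0.6: b = 0.18, shift 0.18/0.139 = 1.30, rejection 25.5%.

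With the target of 111 per group and r from 0.3 to 0.5:

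| d | b (SD) | Rejection rate |
|---|---|---|
| 0.1 | 0.03–0.05 | 6–7% |
| 0.2 | 0.06–0.10 | 7–12% |
| 0.3 | 0.09–0.15 | 10–20% |
| 0.5 | 0.15–0.25 | 20–46% |

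**3. Does the bootstrap help?**

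A percentile bootstrap was simulated on lognormal costs (assumed log-SD 0.8, 111 per group, 1000 trials, 500 resamples each). It rejected in 4% of trials with no imbalance, 8% at d = 0.2 and r = 0.3, 18% at d = 0.3 and r = 0.5, and 41% at d = 0.5 and r = 0.5. Here r is the correlation on the log scale. Resampling within groups copes with skewness but reproduces the imbalance in every replicate.

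**4. In euros**

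At an assumed cost SD of 15,000 euro, 0.08 × 15,000 = 1,200 and 0.18 × 15,000 = 2,700 euro per patient. The article gives no cost SD, so these amounts only show scale.

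**The case against.** The strongest reply is that the article never says the economic results will be unadjusted. The ICER formula is the ordinary definition of the ratio and would equally accept adjusted costs and effects. The statement about arithmetic means concerns reporting. The baseline sentence in the Effect analysis section names costs, so its conditional correction may be meant to reach them, and the source cited for the method cannot be seen here. The MANCOVAs are applied at all measurement points and may take in the EQ-5D. Further confounders are to be collected and analysed, and the Discussion admits the risk of bias. A condensed article may also leave model details to a fuller document.

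Much of this stands. A reader might infer that baseline correction is impossible, or that the plan rules adjustment out. The documents support neither: correction on NIHSS, age, co-morbidity, Barthel or Rankin is feasible, and the clause does not limit itself to baseline values of the same variable.

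What does not fall is narrower. The Economic analysis section sets out its test, estimator and resampling in some detail and includes no adjustment. The clause that might supply one is conditional and names neither variables nor method. The baseline cost comparison that it follows has no scheduled data.

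**Conclusion.** The point holds in limited form and should be corrected. Followed as written, the plan would test costs and build the ICER, plane and acceptability curve in a non-randomised comparison without any specified case-mix adjustment. The conditional correction cannot draw on baseline cost, EQ-5D or SA-SIP30, but it can draw on other baseline variables.

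Neither the size nor the direction of any bias is known. The 9% to 25% error rates and the 1,200 to 2,700 euro depend entirely on the assumed imbalance, correlation and cost SD. With an imbalance of 0.1 SD the rate stays near nominal, at 6% to 7%. A reader might take these figures as the expected error of this study. The article contains nothing that would support that, because it reports no imbalance, no severity-cost correlation and no cost SD.

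**What to change.** 1. Base the primary incremental costs, QALYs and SA-SIP30 difference on estimates adjusted for prespecified covariates that are already collected: age, sex, NIHSS, T0 Barthel and Rankin, co-morbidity and socio-economic status. Regression or an equivalent method would serve.
2. Refit the adjustment in each bootstrap replicate, and derive the ICER, plane and acceptability curve from the adjusted differences. Report the unadjusted bootstrap as secondary.
3. Replace the promised baseline comparison of costs with a comparison on the covariates measured at T0. State plainly that no baseline cost, utility or SA-SIP30 value is available.

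No new data are needed. The cost is some extra programming, with the bootstrap moved from the planned spreadsheet to a statistics package.
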